#### 2.2.3. Sample Size

Power calculations were performed for the primary outcome variable, i.e., the between groups difference in systolic blood pressure. This showed that a total sample size of 45 will be necessary to provide 80% power to detect a minimally important clinical difference (MCID) of 6 mmHg between groups [40], with a projected standard deviation of 5.5 mmHg in each group [41], accounting for a loss to follow up rate of 10%.

### 2.3. Recruitment

It is expected that participants will predominantly be recruited from the UK city of Preston and its surrounding areas. Recruitment will be undertaken by poster promotion across the university campus, at local workplaces and also through advertisements on social media. Interested individuals will be able to contact the research team for further study information and to ask any questions associated with participation in the study. Participants will be invited to attend an eligibility, enrolment and familiarization session at the University of Central Lancashire. Written informed consent will be obtained from those willing to take part.

### 2.4. Dietary Intervention

After the conclusion of their baseline data collection session, participants will be provided with either Montmorency tart cherry, blueberry or placebo concentrate. Participants will be required to consume 30 mL of supplement diluted in 100 mL of water twice daily: once in the morning and again in the evening [27]. All supplementations will be kept refrigerated throughout. According to the manufacturer (ActiveEdge, Hanwell, UK), a 30 mL dose of Montmorency tart cherry concentrate (energy: 102 kcal, carbohydrates: 25 g of which sugars: 18 g, protein: 1.10 g and fibre: 2.6 g) is equivalent to approximately 320 mg of anthocyanins. Similarly, taking into account the manufacturers (ActiveEdge, Hanwell, UK) guidelines, a 30 mL dose of blueberry concentrate (energy: 103 kcal, carbohydrates: 22 g of which sugars: 22 g, protein: 0.2 g and fibre: 0.2 g) is equivalent to approximately 387 mg of anthocyanins. Preparation of the placebo will involve mixing 100% un-flavoured maltodextrin carbs (MyProtein, Cheshire, UK) into drinking water using a magnetic stirrer (Stuart Scientific, UK) and stir bar (Fisher Scientific, Waltham, MA, USA). Then, 666 g of maltodextrin will be added to water to create a litre of placebo concentrate, working out as 20 g of maltodextrin per 30 mL serving, closely matching the Montmorency tart cherry or blueberry concentrates. Even amounts of red and black food colouring will be added to match the colour of the Montmorency tart cherry concentrate and even amount of red, blue and black colouring to match the colour of the blueberry supplement. Either cherry or blueberry flavdrops (1 mL) (MyProtein, UK) will then added to match the required flavour. A 30 mL dose of placebo concentrate (100 kcal, carbohydrates 25 g of which sugars: 0 g, protein: 0 g and fibre 0 g) contains 0 mg of anthocyanins. This method of placebo preparation has been shown by previous intervention trials to provide an effective blinding strategy [42].

Throughout the study, the participants will be encouraged to maintain their habitual diet and exercise routines and asked to refrain from consuming any multivitamin or antioxidant supplements [24]. For their post-intervention data collection session, all participants will be asked to return any un-used supplementation to the laboratory in order to determine the actual amount of supplement/placebo that was consumed (mL), and the % compliance in each group will be reported. Furthermore, in order to examine blinding efficacy, each participant will be asked which trial arm they felt that they had been allocated to at the conclusion of their post-intervention data collection session. In both groups loss to follow up will be monitored, as will be any adverse events.

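### The protocol gives two incompatible carbohydrate contents for one placebo serving (20 g by recipe, 25 g as listed), and its matching claim rests on the 20 g figure

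*Protocol article*

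**What the plan says.** All the relevant statements are in section 2.4 (Dietary Intervention) of the protocol article.

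- **Ingredient:** "Preparation of the placebo will involve mixing 100% un-flavoured maltodextrin carbs" into water. Colouring and 1 mL of flavour drops are the only other additions named.
- **Recipe:** "666 g of maltodextrin will be added to water to create a litre of placebo concentrate".
- **Content by recipe, with the matching claim:** "working out as 20 g of maltodextrin per 30 mL serving, closely matching the Montmorency tart cherry or blueberry concentrates".
- **Content as listed:** "A 30 mL dose of placebo concentrate (100 kcal, carbohydrates 25 g of which sugars: 0 g, protein: 0 g and fibre 0 g").
- **Tart cherry, per 30 mL:** "energy: 102 kcal, carbohydrates: 25 g of which sugars: 18 g, protein: 1.10 g and fibre: 2.6 g".
- **Blueberry, per 30 mL:** "energy: 103 kcal, carbohydrates: 22 g of which sugars: 22 g, protein: 0.2 g and fibre: 0.2 g".
- **Schedule:** "Participants will be required to consume 30 mL of supplement diluted in 100 mL of water twice daily"; section 1.1 gives the duration as 20 days.

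**The concern.** One serving cannot contain both 20 g and 25 g of carbohydrate when maltodextrin is its only stated source. Whoever prepares the placebo cannot satisfy both statements, and a reader cannot tell which product the control arm received. The matching claim is attached to the 20 g figure, which is the one further from the juices in energy and from tart cherry in carbohydrate.

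The placebo is the comparator for the hypotheses of benefit in section 1.2. Several secondary outcomes (body mass and composition, carbohydrate and fat oxidation, glucose, triglycerides) are ones where unequal carbohydrate or energy between arms is a competing explanation. How comparable the control is on those outcomes therefore depends on a figure that the protocol leaves in two versions.

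**Working it through.** **Inputs.** From section 2.4: 666 g/L; 30 mL per serving; two servings a day; placebo listed at 25 g and 100 kcal; cherry at 25 g and 102 kcal; blueberry at 22 g and 103 kcal. From section 1.1: 20 days, hence 2 × 20 = 40 servings. From section 2.5.3: 4 kcal/g for carbohydrate, a factor given there for substrate oxidation and borrowed here for product energy.

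**1. Reproduce the plan's own figures.**
- Recipe: 666 × 0.030 = 19.98 g. The stated 20 g is reproduced.
- Listing: 25 × 4 = 100 kcal. The listed 25 g and 100 kcal agree with each other.

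**2. Compare the two.**
- Energy by recipe: 19.98 × 4 = 79.9 kcal.
- Recipe minus listing: 19.98 − 25 = −5.02 g (−20%), and 79.9 − 100 = −20.1 kcal.
- Concentration needed for 25 g: 25 / 0.030 = 833 g/L, not 666.
- Energy density needed to get 100 kcal from the recipe: 100 / 19.98 = 5.0 kcal/g, above the factor of 4.

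Nothing else in the text supplies the missing 5 g. Rounding cannot do it, 1 mL of flavour drops cannot hold 5 g of carbohydrate, and the listing gives zero sugars, protein and fibre.

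**3. Placebo against the juices, per serving, using the listed juice values.**

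| Placebo version | Carbohydrate vs cherry | Energy vs cherry | Carbohydrate vs blueberry | Energy vs blueberry |
|---|---|---|---|---|
| Recipe (19.98 g, 79.9 kcal) | −5.0 g (−20%) | −22.1 kcal (−22%) | −2.0 g (−9%) | −23.1 kcal (−22%) |
| Listing (25 g, 100 kcal) | 0 g | −2 kcal (−2%) | +3 g (+14%) | −3 kcal (−3%) |

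**4. Sensitivity of the energy gap.** Step 3 sets a calculated placebo value against listed juice values. Taking 4 kcal/g for protein as well (an assumption) and ignoring fibre:
- Blueberry: 22 × 4 + 0.2 × 4 = 88.8 kcal, not 103. The gap to the recipe placebo is 88.8 − 79.9 = 8.9 kcal, about 9 rather than 23.
- Cherry: 25 × 4 + 1.1 × 4 = 104.4 kcal, close to the listed 102. The gap is 24.5 kcal rather than 22.1, so it hardly moves.

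**5. Over the course, if the recipe is what is made.**
- Cherry: 22.08 × 40 = 883 kcal (about 44 kcal a day).
- Blueberry: 8.88 × 40 = 355 kcal to 23.08 × 40 = 923 kcal (about 18 to 46 kcal a day).

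**The case against.** The strongest reply is that this may be one mistyped figure with little consequence. If the listing describes the product, energy matches both juices within 3%. Even by the recipe, carbohydrate is only 2 g below blueberry. The energy gap is small: 883 kcal at the protocol's 9 kcal/g for fat is about 98 g, or 0.1 kg, over 20 days. Visits are fasted, and habitual diet is encouraged rather than controlled. All of this stands and limits the size of the point. It does not remove the contradiction: both figures are printed and only one can be right. Nor is this detail left to a fuller document.

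Three stronger readings are tempting, and the document does not support them.

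- **That benefits would be wrongly credited to the fruit.** By the recipe the placebo arm receives less energy and carbohydrate. Extra energy in the juice arms could as well work against the hypothesised improvements and mask a benefit, which is arguably the likelier result. The document does not settle the direction.
- **That the placebo is mismatched on sugars.** Its 0 g of sugars, against 18 g and 22 g in the juices, is openly listed, and no match on sugars is claimed. That is a disclosed design choice.
- **That the primary outcome is compromised.** Nothing in the document links this gap to systolic blood pressure.

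**Conclusion.** The point holds as an internal contradiction in the specification of the control product: 20 g against 25 g of carbohydrate per serving, a 20% difference. That conflict needs no assumption beyond multiplication. The 80 kcal figure for the recipe rests on 4 kcal/g.

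Whether the placebo matches the juices depends on which version is made. By the recipe, the clear gaps are to cherry, in both carbohydrate and energy. The carbohydrate gap to blueberry is modest, and its energy gap is uncertain within about 9 to 23 kcal. By the listing, energy matches closely and the only visible carbohydrate difference is 3 g above blueberry. What is at stake is the comparability of the control on secondary metabolic outcomes. The document does not allow a choice between the two compositions.

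**What to change.** Reconcile the recipe with the composition listing in section 2.4 before product is made, so that grams per litre, grams per serving and energy per serving agree. State the carbohydrate and energy content actually delivered, with energy for all three products worked out on one stated basis. Limit the matching claim to the components that then match. If product has already been made, report the content delivered.

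The cost is a line of text, or a recipe correction before manufacture. Once participants have been dosed, a discrepancy can be disclosed but not repaired.

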### 2.5. Data Collection

#### 2.5.1. Laboratory Visit Data

All measurements will be made at University of Central Lancashire’s physiology laboratory and will be undertaken in an identical manner on two occasions, i.e., baseline and post-intervention. The laboratories housed by the University of Central Lancashire are fully accredited by the British Association for Sport and Exercise Sciences, illustrating that they have undergone meticulous inspection and evidenced that; all instrumentation is well maintained in terms of reliability, validity and routine servicing, staff have the appropriate professional and vocational qualifications and that the requisite operational procedures for health and safety are met.

#### 2.5.2. Anthropometric Measurements

Anthropometric measures of mass (kg) and stature (m) (without shoes) will be used to calculate body mass index (kg/m^2^). Stature will be measured using a stadiometer (Seca, Hamburg, Germany) and mass will be measured using weighing scales (Seca 875, Hamburg, Germany). In addition, body composition will be examined using a phase-sensitive multifrequency bioelectrical impedance analysis device (Seca mBCA 515, Hamburg, Germany) [43], allowing percentage body fat (%) and fat mass (kg) to be quantified. Finally, waist circumference will be measured at the midway point between the inferior margin of the last rib and the iliac crest and hip circumference around the pelvis at the point of maximum protrusion of the buttocks, without compressing the soft tissues [44], allowing the waist-to-hip ratio to be quantified.

#### 2.5.3. Energy Expenditure and Substrate Oxidation

Respiratory gases will be collected throughout testing using a gas analysis system (MetaLyser 3B system, Cortex Biophysic, Leipzig, Germany). The University of Central Lancashire laboratory is air-conditioned, allowing a fixed ambient temperature of 20 °C to be maintained throughout. To quantify resting energy expenditure and substrate oxidation, participants will lay supine for a period of 20 min and data will be extracted and averaged over the final 17 min [45]. Resting fat and carbohydrate oxidation rates (g/min) will be quantified using established stoichiometric formulae (Equations (1) and (2)), assuming negligible protein utilization [46]. The amounts of each substrate expressed in g/min will be multiplied by 4 for carbohydrates and by 9 for fats [47]. These values will then be summed and subsequently multiplied by 1440 (i.e., the number of minutes per day), allowing daily energy expenditure (kcal/day) to be quantified and the percentage contribution (%) of each substrate to resting energy expenditure to be calculated.

In addition, carbohydrate and fat oxidation rates (g/min) and also the percentage contribution (%) of these substrates to energy expenditure will also be examined, during moderate intensity physical activity. Participants will walk on a treadmill (hp Cosmos Pulsar, Nussdorf, Germany) at a velocity of 4.5 km/h for a period of 6 min [47]. This walking velocity has reliably been shown to correspond to moderate exercise intensities [48]. Data will be averaged over the last minute of the 6 min test [47].
(1)$$\mathrm{Carbohydrate}\;\left(g/min\right)=4.344\times {\mathrm{VCO}}_{2}-3.061\times {\mathrm{VO}}_{2}$$
(2)$$\mathrm{Fat}\;\left(g/min\right)=1.695\times {\mathrm{VO}}_{2}-1.701\times {\mathrm{VCO}}_{2}$$

#### 2.5.4. Haematological Testing

Capillary blood samples will be collected by finger-prick using a disposable lancet after cleaning with a 70% ethanol wipe. Capillary triglyceride, total cholesterol and glucose levels (mmol/L) will immediately be obtained using three handheld analysers (MulticareIn, Multicare Medical, Washington, DC, USA) and capillary haemoglobin levels (g/L) using a single handheld analyser (HemoCue, Ängelholm, Sweden). From these outcomes, LDL cholesterol (mmol/L) will firstly be quantified using the Anandarja et al., [49] formula using total cholesterol and triglycerides as inputs. In addition, high-density lipoprotein (HDL) cholesterol (mmol/L) will also be calculated by re-arranging the Chen et al., [50] equation to make HDL the product of the formulae. Both of these approaches have been shown to have excellent similarity to their associated lipoprotein values examined using immunoassay techniques r = 0.948–0.970 [47,48]. The ratios between total and HDL cholesterol and between LDL and HDL cholesterol levels will also be determined in accordance with Millán et al. [51].

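### HDL is not measured: derived HDL and both HDL ratios are fixed functions of total cholesterol and triglycerides and hold no HDL information beyond those two

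*Protocol article*

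**What the plan says.** Section 2.5.4 (Haematological Testing) of the protocol article lists what is read from the finger-prick sample: "Capillary triglyceride, total cholesterol and glucose levels (mmol/L) will immediately be obtained using three handheld analysers", and "capillary haemoglobin levels (g/L) using a single handheld analyser". These are the only blood measurements in the document.

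The lipoproteins are then calculated. "From these outcomes, LDL cholesterol (mmol/L) will firstly be quantified", by a published "formula using total cholesterol and triglycerides as inputs" (reference [49]). HDL follows by rearranging another published "equation to make HDL the product of the formulae" (reference [50]). Two further indices are built on these values: "The ratios between total and HDL cholesterol and between LDL and HDL cholesterol levels will also be determined".

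In support, the section says that both approaches "have been shown to have excellent similarity to their associated lipoprotein values" obtained by immunoassay, with r = 0.948–0.970, and cites [47,48].

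Section 2.1 makes the haematological indices secondary outcomes, compared between groups. Section 2.7 applies a baseline-adjusted linear mixed model to all outcome measures, with a mean difference, a 95% confidence interval and a 0.05 significance level.

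**The concern.** An outcome labelled HDL should depend on something in the blood sample that responds to HDL separately from the other lipids. Here nothing does. Each participant supplies two lipid readings, yet the plan yields six lipid results: TC, TG, LDL, HDL, TC:HDL and LDL:HDL. Three of the six carry HDL in their name.

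The Introduction names low HDL as a feature of cardiometabolic syndrome, and section 1.2 predicts that both juices improve cardiometabolic parameters. A significant result on derived HDL or on either ratio would naturally be read as an HDL benefit, separate from and additional to any TC or TG result. The data could not support that reading. Equally, a real redistribution between HDL and the other cholesterol fractions would leave no trace.

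The calculation route is fixed in this document, so it is not a detail left to an analysis plan. No analysis method can recover information that was not collected.

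**Working it through.** The plan gives no figure to reproduce. The question is what the derived outcomes can identify, and substitution answers it.

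**Inputs (section 2.5.4)**

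- Measured lipids: TC and TG. Glucose and haemoglobin are also measured, but neither is a lipid.
- LDL: calculated first, from TC and TG.
- HDL: the output of a second equation after rearrangement.
- Measured LDL or HDL: none anywhere in the document.

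**Step 1, LDL.** Write LDL_calc = f(TC, TG), where f is the first cited formula.

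**Step 2, HDL.** Rearranging an equation so that HDL becomes its output requires a value for whatever that equation originally predicted. Write HDL_calc = g(TC, TG, LDL). Feeding in LDL_calc is an inference from the order of the calculations and from the absence of any other LDL. Then

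HDL_calc = g(TC, TG, f(TC, TG)) = h(TC, TG).

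If the second equation needs only TC and TG and no LDL, the result is again a function of TC and TG. The conclusion therefore does not depend on the LDL step.

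**Step 3, ratios.** TC:HDL = TC / h(TC, TG), and LDL:HDL = f(TC, TG) / h(TC, TG). Both are functions of TC and TG alone.

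**Step 4, what a change in true HDL does.**

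- *True HDL changes by δ, TC and TG unchanged.* Other cholesterol fractions move by −δ in total. The change in HDL_calc is h(TC, TG) − h(TC, TG) = 0 for every δ. Both ratios also change by 0.
- *True HDL rises by δ and nothing else changes.* TC rises by δ, and HDL_calc moves by h(TC + δ, TG) − h(TC, TG). If LDL had risen by δ instead, with HDL unchanged, TC would again be TC + δ and HDL_calc would move by exactly the same amount. The derived value cannot tell the two cases apart.

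No coefficients enter these steps, and linearity is not assumed.

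**Step 5, the support offered.** The correlation is attached to both approaches. A good forward prediction, with HDL among the inputs, does not establish that the same equation solved for HDL is accurate, least of all when a calculated value replaces the measured one. As a side note, the two equations carry references [49] and [50], whereas the correlation is cited to [47,48]. Section 2.5.3 uses [47] for the substrate energy factors and the treadmill test, and [48] for walking intensity.

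**The case against.** A reader might infer that derived HDL holds no HDL information at all. The documents do not support that. HDL cholesterol is part of TC, so derived HDL may correlate indirectly with true HDL, and TC:HDL still contains a measured TC. What stands is narrower: nothing about HDL beyond what TC and TG already say. For the same reason, a true HDL effect is certain to be missed only if TC and TG stay unchanged. Otherwise it may reach the derived value, possibly distorted.

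A reader might also want to say which of TC or TG drives derived HDL, and how strongly. That needs coefficients, and the article prints neither equation. Any such statement would rest on assumed values, so none is made here.

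The make-up of the second equation and the use of calculated LDL in it are inferences. This objection is correct but does not change the result, since every available lipid input comes from TC and TG.

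The [47,48] citation could be a numbering slip. It does not show that validation is lacking, and what the correlation covers cannot be checked from the article.

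LDL is also a fixed function of TC and TG, so keeping it while deleting HDL may look uneven. The difference is that the LDL formula is used forwards with measured inputs, whereas HDL comes from an inverted equation. LDL still adds no independent evidence and should be labelled accordingly.

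Finally, HDL is not named as an outcome in sections 1.2 or 2.1. It falls under the haematological indices, and nothing commits the authors to an HDL-specific conclusion. That limits the weight of the point but does not remove it, because section 2.7 covers all outcome measures. The limitations in section 4 do not mention the issue.

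**Conclusion.** The point holds as a secondary-outcome correction. As section 2.5.4 is written, derived HDL, TC:HDL and LDL:HDL are deterministic functions of TC and TG. They have no HDL content beyond those two readings, and their response to a change in true HDL at fixed TC and TG is exactly 0. An apparent HDL effect would be TC or TG movement counted again, in up to three further results.

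The conclusion assumes only that the derivation uses the lipid quantities that the section makes available: measured TC, measured TG and the LDL calculated from them. It does not depend on the coefficients. Systolic blood pressure, the sample size and the primary analysis are unaffected.

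**What to change.** - Remove derived HDL, TC:HDL and LDL:HDL from the secondary outcomes and from any conclusion.
- Keep measured TC and TG as the lipid outcomes.
- Report LDL only as an estimate calculated from TC and TG, and state that it is not evidence independent of them.
- Check the references attached to the correlation, and limit the validation statement to what those sources examined.

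HDL could return as an outcome only if it were measured directly, which would be an addition to the present plan.

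The cost is wording in the protocol, together with the ethics re-review and registry amendment that section 3 requires for protocol changes. Three outcomes are lost, none of which holds independent information. No extra sample or visit is needed.

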#### 2.5.5. Blood Pressure and Resting Heart Rate

Blood pressure and resting heart rate measurements will be undertaken in an upright seated position at the end of the above-described resting energy expenditure test. Both peripheral measures of systolic and diastolic blood pressure and resting heart rate will be measured via a non-invasive, automated blood pressure monitor (OMRON M2, Kyoto, Japan), adhering to the recommendations specified by the European Society of Hypertension [52]. Three readings will be undertaken, each separated by a period of 1 min [53], and the mean of the last 2 readings used for analysis.

#### 2.5.6. Questionnaires

Sleep quality is diminished in patients with cardiometabolic disease [54] and intake of dietary polyphenols [55], and supplementation of Montmorency tart cherry has been demonstrated to enhance sleep quality and symptoms of insomnolence [56,57]. Therefore, general sleep quality will be examined using the Pittsburgh sleep quality index [58], daytime sleepiness using the Epworth Sleepiness Scale [59] and symptoms of insomnolence via the Insomnia Severity Index [60]. These questionnaires will be utilized cooperatively to provide a collective representation of sleep efficacy.

Furthermore, psychological wellbeing is lower in those with cardiometabolic disease [61] and a high intake of dietary polyphenols has been shown to enhance indices of psychological wellbeing [62]. Therefore, general psychological wellbeing will be examined using the COOP WONCA questionnaire [63], depressive symptoms using the Beck Depression Inventory [64] and state/trait anxiety with the State Trait Anxiety Inventory [65]. Once again, these scales will be utilized conjunctively to provide a collective depiction of psychological wellbeing.

